**Methods:**

This study is a single-blind, parallel-group randomized controlled trial. A total of 60 participants scheduled for primary unilateral ACLR will be recruited and randomly allocated to either the experimental group (conventional rehabilitation plus gait retraining) or the control group (conventional rehabilitation only). Gait retraining will commence at 3 weeks post-surgery, lasting for 6 weeks with a frequency of 2–3 sessions per week, each lasting 15–20 min. Data will be collected at baseline (pre-intervention) and at 3 months, 6 months, 1 year, and 2 years postoperatively. Assessment will include three-dimensional gait analysis, surface electromyography (sEMG), isokinetic muscle strength testing, functional magnetic resonance imaging (fMRI), Y-balance test, single-leg hop test, the International Knee Documentation Committee (IKDC) subjective knee evaluation form, Lysholm knee score, and Tegner activity scale. The primary outcome measure is the peak knee flexion moment during walking. Secondary outcomes include cartilage T1*ρ*/T2 values, muscle activation patterns, and subjective functional scores. A repeated-measures analysis of variance (ANOVA) will be used to evaluate the intervention effects on the outcome measures.

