#### Inclusion and exclusion criteria

A total of 60 patients scheduled for ACLR will be recruited. After enrollment, participant information will be entered into the RED Cap system, and participants will be randomly assigned to two groups (experimental group, *n* = 30; control group, *n* = 30) using a mixed block randomization method. This is a single-blind randomized controlled trial; participants will not be informed of their group assignment or the intervention details prior to the intervention. Baseline information and data will be collected preoperatively. After the study procedures have been fully explained and understood, written informed consent will be obtained from all participants at the Department of Sports Medicine, Peking University Third Hospital. All data collection and interventions will be conducted at the same department.

Inclusion Criteria: (1) age 18–35 years; (2) diagnosis of ACL rupture confirmed by MRI; (3) first-time unilateral ACL rupture scheduled for reconstruction at our institution; (4) body mass index (BMI) within the normal range of 18.5–23.9 kg/m^2^ (to exclude the confounding effect of obesity on joint loading); (5) time since injury less than 6 months; (6) affected knee has passed the acute phase, with no significant swelling, pain, inflammation, or range of motion limitation, and basic joint mobility is restored.

Exclusion Criteria: (1) history of musculoskeletal injury or surgery on the contralateral lower limb; (2) time since ACL injury 6 months; (3) cartilage injury with Outerbridge grade III or IV; (4) concurrent meniscal tear requiring meniscal repair during ACLR; (5) concomitant severe injury to the posterior cruciate ligament, medial collateral ligament, or lateral collateral ligament; (6) presence of metabolic syndrome (obesity, dyslipidemia, diabetes, etc.), immune system diseases affecting articular cartilage, or severe cardiovascular or cerebrovascular diseases; (7) unwillingness to receive the allocated treatment.

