### Statistical analysis

The primary analysis will employ a mixed-effects model to account for within-subject correlations across repeated measures during the 2-year follow-up and to handle potentially missing data at random. All statistical tests will be performed with a significance level set at *α* = 0.05. A repeated-measures two-way analysis of variance (ANOVA) will be used to evaluate the interaction effects between group (experimental vs. control) and time (baseline, 3 months, 6 months, 1 year, and 2 years) on cartilage biochemical characteristics derived from functional MRI (T1*ρ*/T2 values) and on gait parameters. For multiple comparisons, the Bonferroni correction will be applied. For EMG data, repeated-measures ANOVA will be used to assess the differences in muscle activation patterns before and after gait retraining, thereby exploring the neuromuscular control mechanisms underlying the effects of gait retraining on gait biomechanics. To control the false discovery rate (FDR) when comparing MRI parameters across 10 cartilage subregions and multiple time points, the FDR method will be applied with the threshold set at 0.05. Missing data will be assumed to be missing at random (MAR) and will be addressed using the mixed-effects model without imputation or deletion. For the analysis populations, the primary analysis will follow the intention-to-treat (ITT) principle, including all participants as originally randomized. Sensitivity analysis will be performed using a per-protocol (PP) set, including only participants who completed the full intervention and all follow-up assessments. Effect sizes will be reported as partial eta-squared (*η*^2^). Outliers, defined as values exceeding ±3 standard deviations from the group mean, will be excluded and reanalyzed in a sensitivity analysis.

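### The EMG analysis is worded as a change across gait retraining, which only one arm receives, so it cannot separate retraining from surgery, recovery and the shared rehabilitation

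*Protocol article*

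**What the plan says.** The abstract of the protocol article lists the secondary outcomes: "Secondary outcomes include cartilage T1*ρ*/T2 values, muscle activation patterns, and subjective functional scores". Surface EMG of the quadriceps, hamstrings, tibialis anterior and gastrocnemius during walking is described under Gait analysis.

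The Statistical analysis section treats the outcomes differently:

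- For MRI and gait, a two-way repeated-measures ANOVA will "evaluate the interaction effects between group (experimental vs. control) and time (baseline, 3 months, 6 months, 1 year, and 2 years"), and this applies "on cartilage biochemical characteristics derived from functional MRI (T1*ρ*/T2 values) and on gait parameters".
- For EMG there is a separate sentence: "repeated-measures ANOVA will be used to assess the differences in muscle activation patterns before and after gait retraining". Its stated purpose is "exploring the neuromuscular control mechanisms underlying the effects of gait retraining on gait biomechanics". It names no group factor.

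On timing, the section on inclusion and exclusion criteria states: "Baseline information and data will be collected preoperatively". Study design and Measurement procedures place the later assessments at 3 months, 6 months, 1 year and 2 years for both groups. Gait retraining is given to the experimental group only. It starts 3 weeks after surgery and runs for 6 weeks. Both groups follow the conventional rehabilitation programme in Table 2, except that the experimental group leaves out its walking component on retraining days.

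**The concern.** A change measured across retraining exists, in any literal sense, only in the arm that is retrained. A repeated-measures ANOVA of that change tests whether muscle activation differs between visits. It does not test whether the change differs between randomised groups. Yet the sentence uses the result to explain effects of retraining, which is a causal reading that only the control arm can support.

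The time points make this worse. The last measurement before retraining is preoperative, on the ACL-deficient knee, and the first one afterwards is at 3 months. The article schedules no assessment between surgery and the start of retraining. Much besides retraining happens in that interval, and some of it acts directly on the recorded muscles: Table 2 includes quadriceps and hamstring contractions, hamstring curls and mirror-guided walking. If EMG changes because of any of this, the stated contrast will show a change whether or not retraining does anything.

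**Working it through.** **1. What the two contrasts estimate.** Let R be the mean change from baseline caused by surgery, recovery and conventional rehabilitation, taken as equal in both arms, and let T be the added effect of retraining.

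- Experimental arm, after minus before: R + T.
- Control arm, over the same visits: R.
- Difference between arms in change (group × time): (R + T) − R = T.

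The first quantity equals T only if R = 0. Nothing in the article suggests that R is zero.

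**2. The interval.** Retraining occupies postoperative weeks 3 to 9 (3 + 6 = 9). The before-after interval runs from before surgery to 3 months. It therefore also includes the operation, the 3 weeks before retraining starts and the weeks between its end and the visit.

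**3. The plan's own figures.** The article gives no sample size, mean, SD or correlation for EMG. Its only calculation is for peak knee flexion moment, and it reproduces:

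- σ = √((0.09² + 0.11²)/2) = 0.1005 and δ = 0.28 − 0.20 = 0.08.
- n = 2σ²(z for α/2 + z for β)²/δ² = 24.77, rounded up to 25 per group; 25 × 1.2 = 30.
- Standardised difference: 0.08/0.1005 = 0.796, about 0.8.

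These figures are used below only to set n and the top of the range.

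**4. Illustration of size.** Inputs:

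- n = 30 as randomised, or 30 × (1 − 0.20) = 24 after the stated dropout.
- T = 0, so retraining has no effect.
- R = 0.3, 0.5 or 0.8 SD. These are assumed. The top value borrows the size of the knee flexion moment change, which is a different outcome.
- Before-after correlation ρ = 0.5, range 0.3 to 0.7. Also assumed.
- Two-sided α = 0.05.

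For a paired test, the change in units of its own SD is dz = R/√(2(1 − ρ)), with noncentrality dz√n. At R = 0.8, ρ = 0.5 and n = 24, dz = 0.8/√1 = 0.8 and the noncentrality is 0.8 × √24 = 3.92. The critical t is 2.07 and the rejection rate about 0.96. Simulation with 20,000 runs per setting gives 0.964 for that case, and overall:

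| Shared recovery R | Paired test, n = 24, ρ = 0.5 (range over ρ) | Paired test, n = 30, ρ = 0.5 (range over ρ) | Group × time |
|---|---|---|---|
| 0 | 5% | 5% | about 5% |
| 0.3 SD | 30% (22–44%) | 36% (27–54%) | about 5% |
| 0.5 SD | 65% (52–86%) | 75% (61–92%) | about 5% |
| 0.8 SD | 96% (89–100%) | 99% (95–100%) | about 5% |

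The group × time test holds its level in every setting because R cancels.

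**The case against.** **The control arm is not expressly excluded.** A reader might infer that the control arm's EMG data are to be discarded. The article does not say so. The abstract states in general terms that "A repeated-measures analysis of variance (ANOVA) will be used to evaluate the intervention effects on the outcome measures", and EMG is collected under the Gait analysis heading, so the gait parameters in the group × time sentence could be stretched to include it. This stands as a limit on the claim: the wording describes a within-arm contrast, but it does not prove that controls will be left out. It does not remove the problem. The section spells out group × time where it intends it and then gives EMG a different contrast. Even with controls in the model, a difference between visits averaged over arms would still contain R.

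**This is a condensed article.** Strength, balance, hop tests and subjective scores have no specific analysis either, and a full plan may supply them. That answers a complaint about a missing group term. It does not answer one about a contrast that is stated and cannot support the inference attached to it.

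**The purpose is exploratory.** The sentence speaks of exploring mechanisms, which lowers the stakes. But EMG remains a named secondary outcome, and the change is still interpreted as a result of retraining.

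**The abstract.** A reader might infer that calling baseline pre-intervention in the abstract conceals its timing. It does not: a preoperative measurement does precede the intervention, and the Methods state the timing openly.

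**The percentages.** A reader might take 96% as the expected false-positive rate for this trial. It is one high-end scenario with an assumed recovery and correlation. It also uses a single paired test, whereas the plan has a repeated-measures ANOVA over several visits with Bonferroni correction for multiple comparisons. The figures show the mechanism and its possible range; they do not forecast the trial's error rate.

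**Conclusion.** The point holds for the contrast as worded. EMG is given a comparison across retraining, while MRI and gait parameters are given group × time. With a preoperative baseline and a first follow-up at 3 months, the EMG comparison cannot distinguish retraining from surgery, recovery and the conventional rehabilitation of both arms.

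With no retraining effect, shared recovery of 0.3 to 0.8 SD would make a simple before-after test significant in about 22–100% of trials, against about 5% for group × time. Those figures rest on assumed recovery sizes and correlations and on equal recovery in both arms. The direction of the problem depends only on recovery not being zero.

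The defect affects a secondary outcome with an exploratory aim and leaves the primary outcome untouched. It should be corrected because the stated inference does not follow from the stated analysis.

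**What to change.** Replace the EMG sentence in Statistical analysis with one to this effect: each EMG measure will be analysed with the same group × time contrast as the gait parameters, within the mixed-effects model; the between-group difference in change from baseline is the estimate of the retraining effect; within-arm change between visits is reported as description only.

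The gait parameters are the right model to copy for the contrast. The article does not describe a baseline-adjusted model for them, and this change does not need one. The abstract needs no edit on this point.

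The cost is one sentence. Both arms are already scheduled for assessment at every visit, so no further measurements or patients are required.

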### Participants and recruitment

#### Sample size calculation

The primary outcome measure is the peak knee flexion moment during walking, a key biomechanical indicator of cartilage degeneration (21). A significant difference in this measure will be considered statistically meaningful. Based on preliminary results, the mean peak knee flexion moment before training in ACLR patients is 0.20 BW·BH, with a standard deviation of 0.09. After training, the mean peak knee flexion moment is 0.28 BW·BH, with a standard deviation of 0.11 Nm/kg/m. Using the formula for sample size estimation for two independent samples, $n=\frac{2\sigma^{2}{\left(Z_{\alpha /2}+Z_{\beta }\right)}^{2}}{\delta^{2}}$, with *α* = 0.05 and *β* = 0.2,among $\sigma =\sqrt[{2}]{\frac{\sigma_{1}^{2}+\sigma_{2}^{2}}{2}}$, $\delta =\bar{X_{1}}-\bar{X_{2}}$, the required sample size for each group was calculated to be 25.Accounting for a 20% dropout rate, 30 participants per group will be recruited. The required sample size corresponds to a Cohen's d of 0.8, indicating a large effect size.

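### The outlier sentence leaves open whether valid extreme values leave the primary analysis, and its cut-off around each group's own mean is anti-conservative for skewed outcomes

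*Protocol article*

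**What the plan says.** All the relevant text is in the Statistical analysis section of the protocol article.

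- Outliers: "Outliers, defined as values exceeding ±3 standard deviations from the group mean, will be excluded and reanalyzed in a sensitivity analysis".
- Analysis population: "the primary analysis will follow the intention-to-treat (ITT) principle, including all participants as originally randomized". A per-protocol set is named as a sensitivity analysis.
- Missing data: "Missing data will be assumed to be missing at random (MAR) and will be addressed using the mixed-effects model without imputation or deletion".
- Level: "All statistical tests will be performed with a significance level set at *α* = 0.05".

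The outlier sentence names no outcome, so it appears to cover gait, EMG and MRI measures alike. It does not ask for evidence that a flagged value is an error.

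**The concern.** The sentence has two readings.

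- **(a)** Values beyond 3 SD are removed, and a sensitivity analysis then revisits the question.
- **(b)** The removal takes place only inside the sensitivity analysis.

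Two analysts could follow the text faithfully and report different primary results, and the choice could be made after the data are seen.

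Under (a), a knee that responds very well or very badly is treated as an error. The deleted value is then missing because of its own size, which is not missing at random, although the mixed model relies on that assumption.

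Under both readings the cut-off depends on the arm. An arm with several large values has a large SD and keeps them, while an arm with one large value loses it. This can widen a chance difference while the within-arm variance shrinks.

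**Working it through.** **1. The plan's own figure.** The article gives no number for the outlier rule. The figures borrowed below come from its Sample size calculation section: mean 0.20 and SD 0.09 before training, 0.28 and 0.11 after, 30 per group. They reproduce the stated sample size: σ² = (0.09² + 0.11²)/2 = 0.0101, δ = 0.08, n = 2 × 0.0101 × (1.96 + 0.84)²/0.08² ≈ 24.8, rounded up to 25 per group. This point does not disturb that result.

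**2. How often the rule acts on normal data.** The mean and SD are estimated from the same 30 values, so the normal tail area of 0.0027 is too large. With r = 3√30/29 = 0.567, the equivalent t statistic is 0.567 × √28/√(1 − 0.567²) ≈ 3.64 on 28 df. The two-sided probability is 0.0011 per value.
- Primary outcome, complete data: 60 × 5 = 300 values, 300 × 0.0011 ≈ 0.3 flagged.
- MRI, 10 subregions × 2 maps × 300 = 6,000 values: about 6.6 flagged.
- One visit, 60 values: 1 − (1 − 0.0011)^60 ≈ 6% of comparisons lose at least one value.

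**3. False-positive rate.** Setup: no true difference, 30 per arm, one visit, pooled two-sided t-test at 0.05, one pass of deletion, at least 100,000 simulated trials per shape. Where repeat runs differed through simulation error, the range is shown for the own-arm column.

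| Assumed shape | No deletion | 3 SD around own arm mean | 3 SD around mean of both arms | Trials losing a value (own-arm rule) |
|---|---|---|---|---|
| Normal | 4.9% | 5.2–5.3% | 4.9% | 6% |
| Gamma, mean 0.20, SD 0.09 | 5.0% | 6.3–6.5% | 5.0% | 32% |
| Lognormal, log-SD 0.25 | 5.0% | 6.2–6.3% | 5.1% | 28% |
| Lognormal, log-SD 0.5 | 5.0% | 7.4–7.6% | 5.0% | 61% |
| Exponential | 4.7% | 8.5–8.7% | 4.8% | 72% |
| Lognormal, log-SD 1 | 4.1% | 8.8–8.9% | 4.8% | 92% |

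**4. Which rows are close to the documented spread.** The coefficients of variation are 0.09/0.20 = 0.45 and 0.11/0.28 = 0.39. A gamma with these values gives 6.2 to 6.5%, a lognormal 6.9 to 7.1%. A lognormal with log-SD 0.5 has √(e^0.25 − 1) = 0.53, a little beyond the documented spread. The last two rows lie well beyond it and only show the direction.

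**5. Why the centring matters.** With one cut-off for both arms, deletion does not depend on group labels, and the rate stays at 4.8 to 5.1%. A 3 SD cut-off on residuals from a model with group in it still centres on the arm means. In the same simulation it leaves about 5.4 to 6.1%, so it is only a partial remedy.

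**The case against.** A reader might infer that the sentence flatly contradicts two neighbouring statements. The documents do not support that.

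- The phrase "will be addressed using the mixed-effects model without imputation or deletion" has missing data as its subject. It says nothing about observed extreme values.
- Intention-to-treat is described as "including all participants as originally randomized". That concerns people and arms. In a mixed model a participant who loses one value stays in the assigned arm.
- Reading (b) is at least as natural as (a): the closing phrase can govern both verbs, and the article has just made the all-randomized analysis primary. Under (b) the primary analysis loses nothing.

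A reader might also infer that the primary test runs at 8% or more. That would need reading (a) together with skew beyond the documented spread of the primary outcome. For normal data the effect is negligible.

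Finally, a condensed article may leave the details of outlier handling to an analysis plan that is not shown. That is fair for the visit-by-visit mechanics. It does not cover the two things the article does state: a sentence that does not say what happens to the primary analysis, and a cut-off tied to the group mean.

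**Conclusion.** The point holds as an ambiguity with a poorly chosen cut-off. It does not hold as a contradiction.

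- **Primary inference** is affected only on reading (a). There the harm is loss of valid data because of their size and, if the primary outcome is mildly skewed, a false-positive rate about 1 to 2 percentage points above nominal.
- **The sensitivity analysis** is affected on reading (b): for skewed outcomes it is anti-conservative and so a weak check on robustness.
- **If outcomes are close to normal**, the cut-off has almost no effect on error (about 5.3%), and only the ambiguity remains.

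These sizes rest on assumed distributions and on a single-visit t-test standing in for the repeated-measures mixed model. The direction of the effect does not depend on the particular skewed shape tried.

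**What to change.** Replace the outlier sentence with wording to this effect: *The primary intention-to-treat mixed model uses all observed values, except those shown, by reviewers blind to group, to be measurement errors. A sensitivity analysis repeats the model without values more than 3 SD from the mean, with mean and SD calculated at each visit over both groups combined.*

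The cut-off should not be set around arm means or around residuals from a model that contains group. The change costs one or two sentences of analysis wording, needs no extra participants or data, and should be made before anyone sees outcomes by group.

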### Statement of ethics and consent to participate

The National Bioethics Committee's Review Board granted ethical approval for this research with human participants. Written informed consent will be obtained from all study participants.

## Discussion

Current standardized rehabilitation protocols following ACLR primarily focus on restoring muscle strength, range of motion, and neuromuscular coordination. However, even if these indicators return to normal, abnormal gait biomechanical characteristics still cannot be completely corrected, and specific GRT should be added to restore gait. Therefore, this study aims to address the gap in incorporating specific GRT into post-ACLR rehabilitation programs. By investigating whether GRT can optimize standard rehabilitation, we hope to provide a strategy for preventing or delaying the occurrence and progression of cartilage degeneration. This has important clinical implications for helping athletes and active individuals restore normal gait and prevent secondary injuries.
